### 8.3.4 Documentation and reporting of adverse events

All AEs will be documented in the AE page of the CRF, whether or not the investigator concludes that the event is related to the drug treatment. The following information will be documented for each event:

- Event term (preferably, diagnosis).
- Dates of the beginning and the end of AE.
- Frequency: intermittent, continuous.
- Severity: CTCAE grades
- Causal relationship between the event and administration of study drug or study procedure (not related, conditional, unlikely related, possibly related, probably related, definitely related, not applicable).
- Action concerning study drug (drug withdrawn, dose not changed, dose reduced/increased, unknown, not applicable).
- Outcome of event (recovered, recovering, not recovered, resolved with sequelae, fatal, unknown).
- Seriousness (serious, non-serious).

Information on TEAEs and SAEs will be received by all members of the Study team.

#### 8.3.4.1 SAE reporting

When an SAE occurs through the AE collection period it should be reported according to the following procedure:

As soon as the Investigator is aware of SAE, he/she:

- immediately registers information in patient's medical file,
- immediately (or within 24 hours of first onset or notification of the event) completes and signs the SAE form and sends it to Atlant Clinical by fax or e-mail (e-mail: [[contact]](mailto:[contact]), contact information will also be given in the Investigator study file):

Concerning any safety aspects, the Atlant Clinical medical monitor should be contacted:

Name: [name]

Position: Medical Monitor

[contact]

[contact]

[contact]

e-mail: [[contact]](mailto:[contact]), [[contact]](mailto:[contact]).

In the SAE form the information should be completed as fully as possible but contain at a minimum:

- A short description of the event and the reason why the event is categorized as serious.
- Subject identification number.
- Investigator's name.
- Name of the study drug

In case of SAE, the Sponsor must also be notified either by the Investigator or by Atlant Clinical within 24 hours after the Investigator/CRO is aware of the SAE:

Name: [name]

Position: Senior Medical Advisor

[contact] Ext 182

Tel. (mobile): [contact]

e-mail: [[contact]](mailto:[contact])

Any follow-up information on SAE should be notified within 24 hours via the SAE form (the procedure should be the same as described above). If a non-serious adverse event becomes serious, or if an adverse event becomes a suspected fatal/life-threatening adverse reaction, the procedure should be the same as described above.

For SAEs, the Investigator will send to Atlant Clinical anonymized copies of additional medical documents with relevant information on the event in the same way as described above. Upon SAE completion the final SAE report form should be filled and sent to Atlant Clinical by e-mail: [[contact]](mailto:[contact]) or by [contact]

Atlant Clinical will immediately transmit to the Sponsor the forms and documents received from the Investigator (within 24 hours after the information was received by CRO).

### **8.3.1 Reporting Adverse Events to Subjects**

Subjects will be informed of any severe AEs or SAEs that they experience as part of their participation in this trial.

#### **8.3.1.1 Overdose reporting**

Cases of overdose with any medication without manifested side effects are not considered AEs, but will be documented in an Overdose section of the eCRF. Following information should be included (but not limited to): whether the overdose was suspected or confirmed, whether or not involving study medication, overdose signs and symptoms, action taken, medication/antidote given or not. Any manifested side effects will be considered AEs.

#### **8.3.1.2 Reporting of Pregnancy**

While pregnancy is not considered to be an AE or SAE, any pregnancy complication or elective termination of a pregnancy will be reported as an AE or SAE. A spontaneous abortion is always considered to be an SAE and will be reported as such. In situation when pregnancy occurs during study participation, it should be reported to Atlant Clinical medical monitor (for Sponsor

informing) within 24 hours using the procedure described for SAE reporting. Pregnancy should be recorded on the eCRF and source documents, a specialized Pregnancy Form should be filled.

If a female study participant is pregnant, then further IP intake and all study procedures should be cancelled. The female patient who becomes pregnant during the study will be followed using a Pregnancy Form until the outcome of the pregnancy is known.

Any pregnancies in the partner of a male study participant during the study should also be recorded following authorization from the subject's partner, withdrawal of the male study participant from the study is not required. Pregnancy of the male study participant's partner should also be followed using Pregnancy Form.

For both female subjects and partners of male subjects information about SAEs that occurred during pregnancy with the mother and/or fetus or child should be transmitted to the Sponsor also in case of Study discontinuation.

Pregnancy outcome, including any premature termination, must be reported to the Sponsor. An evaluation after the birth of the child should also be conducted.

### **8.3.2 Responsibility of the Sponsor**

The sponsor will be responsible for reporting all suspected unexpected serious adverse reactions (SUSARs) to regulatory authorities, Investigators and Ethics Committee in accordance with national regulations of Russian Federation. Relative to the first awareness of the event by/or further provision to the Sponsor, SUSARs will be submitted to the regulatory authorities as expedited report within 7 days for fatal and life-threatening events and 15 days for other serious events. Relevant follow-up information will be submitted to a safety report as soon as the information is available. Upon request from regulatory authority, the Sponsor will submit any additional data or information that the agency deems necessary, as soon as possible, but in no case later than 15 calendar days after receiving the request. SAEs that are not SUSARs will be reported to the regulatory authority at least annually in a summary format which includes all SAEs.

The Sponsor will also prepare expedited reports for other safety issues which might alter the current benefit-risk assessment of the study drug or that would be sufficient to consider changes in the study drug administration or in the overall conduct of the trial. The study site also will forward a copy of all expedited reports to its Ethics Committee in accordance with local regulations.

### **8.4 Type and Duration of the Follow-up of Subjects After Adverse Events**

All AEs and SAEs should be followed up until resolution or stabilization. The timelines and procedure for SAE follow-up reports are the same as those for the initial report.

The Investigator must ensure that follow-up of the participant is appropriate to the nature of the event, and that it continues until resolution if deemed necessary.

Any secondary worsening (i.e. from a non-serious adverse event to a serious adverse event) should be notified to the Sponsor without undue delay. Any new information (diagnosis, intensity, measures taken, causality or outcome) regarding an adverse event already reported will be documented in the source document and eCRF.

If the adverse event has not resolved at the participant's final visit in the study, the participant must be followed up suitably and any information on the outcome of the event will be recorded.

### **8.5 Safety data review by DSMB**

An independent Data Safety and Monitoring Board (DSMB, detailed in Section 11.6) will be established and meet at regular intervals as defined by the DSMB Charter after commencing the trial participants recruitment to ensure safety of the intervention by monitoring blinded safety data collected in this Study. The DSMB will meet prior to the start of the Study and at the projected middle of the study recruitment period, it may also meet on an *ad hoc* basis if necessary.

## 9 STATISTICS

### 9.1 Description of the Statistical Methods to be Employed

An overall comprehensive statistical analysis plan (SAP) for this clinical trial (including trial design) will be developed and finalized after trial initiation and before data lock/unblinding.

Sponsor/CRO will be responsible for ensuring all data is entered accurately into the study database. All analyses will be undertaken by Sponsor/CRO following completion of recruitment and data collection phases, all data will be entered into a secure database and after the data cleaning process the database will be locked for analysis. All assessment measures will be scored according to standardized procedures. Creation of derived variables or conversion of variables (log-transformation, Z-scores etc.) will be determined for each sub-analysis. These will be documented in the SAP for each of these smaller sub-analyses.

#### 9.1.1 Descriptive analysis of demography and baseline data

Data on demographics, laboratory results, vital signs, physical examination will be presented using the following descriptive statistics: number of observations, percentages, mean, standard deviation, median, quartiles, minimum and maximum values.

These baseline differences and differences in outcomes at 1, 3, 6 and 9-month follow-up will be summarized using means, standard deviations, medians, quartiles, minimums and maximums.

Baseline value for all parameters is defined as the most recent estimate before first drug intake.

#### 9.1.2 Efficacy analysis

Primary analysis will employ ITT population, sensitivity analyses will be performed using ITT population with LOCF imputations and PP population.

Primary efficacy endpoint: Change in complex attention score, determined using Central Nervous System Vital Signs (CNS-VS) computer cognitive testing system, after 6 months of treatment compared to baseline in the group of patients receiving NeuroAiD II™ (MLC901), compared to the placebo group.

For primary endpoint analysis for each patient, the difference in complex attention scores, determined using CNS-VS computer testing, after 6 months of therapy compared to baseline, will be calculated: the change in complex attention score compared to baseline. Mixed effects model (PROC MIXED) will be used with adjustments for baseline and potential covariates. All timepoints will be used for the model. The participant and site will be used as the random effects. Model selection will be undertaken with each outcome using standard selection heuristics. Covariates will be selected based on improving the overall efficiency of the model. Regardless, baseline and age, gender, time since injury (1-3 months/4-12 months) and study center will be included as covariates in the mixed effects model. Descriptive statistics will be calculated to change in complex attention in each group, as well as mean values obtained by the method of least squares from the mixed effects model.

Superiority of MLC901 over placebo will be claimed if

$H_0: \text{LSM}_T \geq \text{LSM}_R$  is rejected and thereafter

$H_1: \text{LSM}_T < \text{LSM}_R$  is accepted at significance level of 5%,

where  $\text{LSM}_T$  is a Least Square Mean of Change from Baseline of Complex attention score after 6 months of treatment assessed by the mixed model repeated measures analysis in the MLC901 group and  $\text{LSM}_R$  is a Least Square Mean of Change from Baseline of Complex attention score

after 6 months of treatment assessed by the mixed model repeated measures analysis in the Placebo group (lower score of Complex attention is better).

#### Secondary efficacy endpoints

- Changes in the scores for the following cognitive domains: executive functioning, processing speed, memory (visual and verbal) and reaction time, determined by CNS-VS system, after 6 months of treatment compared to baseline, in the NeuroAiD II™ (MLC901) group, compared to the placebo group.
- Change in the Rivermead Post Concussion Symptoms Questionnaire (RPQ) total score, after 6 months of treatment, compared to baseline, in the NeuroAiD II™ (MLC901) group compared to the placebo group.

#### Exploratory efficacy endpoints

- Change in the Health-related quality of life questionnaire (QOLIBRI) total score after 6 months of treatment, compared to baseline, the NeuroAiD II™ (MLC901) group compared to the placebo group.
- Change in the Hospital Anxiety and Depression Scale (HADS) score after 6 months of treatment, compared to baseline, in the NeuroAiD II™ (MLC901) group compared to the placebo group.
- Changes, compared to baseline, in the analyzed parameters (complex attention, executive functioning, processing speed, visual and verbal memory, reaction time, RPQ score, QOLIBRI score, HADS score) 9 months after NeuroAiD II™ (MLC901) treatment initiation with reference to baseline, compared to the placebo group. .

The same approach as for primary endpoint will be used for analysis of secondary efficacy endpoints and exploratory endpoints, and completely similar hypotheses are be formulated as for the analysis of the primary endpoint. Mixed effects models will be used to analyze the change in values from baseline, adjusted for covariates and baseline estimates. No sensitivity analysis will be performed for secondary endpoints. No adjustments will be made for multiple comparisons, hypotheses will be tested hierarchically, hypothesis testing by secondary endpoints will be taken into account if statistically significant differences between groups for the primary endpoint are confirmed.

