|  | 
Primary analysis will employ the Intention-to-treat population (ITT population), sensitivity analyses will be performed using ITT population with LOCF imputations and PP population.
 
Primary efficacy endpoint: Change in complex attention score, determined using Central Nervous System Vital Signs (CNS-VS) computer cognitive testing system, after 6 months of treatment compared to baseline in the group of patients receiving NeuroAiD II™ (MLC901), compared to the placebo group.
 
For primary endpoint analysis for each patient, the difference in complex attention scores, determined using CNS-VS computer testing, after 6 months of therapy compared to baseline, will be calculated: the change in complex attention score compared to baseline. Mixed effects model (PROC MIXED) will be used with adjustments for baseline and potential covariates. All timepoints will be used for the model. The participant and site will be used as the random effects. Model selection will be undertaken with each outcome using standard selection heuristics. Covariates will be selected based on improving the overall efficiency of the model. Regardless, baseline and age, gender, time since injury (1-3 months/4-12 months) and study center will be included as covariates in the mixed effects model. Descriptive statistics will be calculated to change in complex attention in each group, as well as mean values obtained by the method of least squares from the mixed effects model.
 
Superiority of MLC901 over placebo will be claimed if
 
H0: <math>LSM_T \geq LSM_R</math> is rejected and thereafter
 
H1: <math>LSM_T < LSM_R</math> is accepted at significance level of 5%,
 
where <math>LSM_T</math> is a Least Square Mean of Change from Baseline of Complex attention score after 6 months of treatment assessed by the mixed model repeated measures analysis in the MLC901 group and <math>LSM_R</math> is a Least Square Mean of Change from Baseline of Complex attention score after 6 months of treatment assessed by the mixed model repeated measures analysis in the Placebo group (lower score of Complex attention is better).
 
Secondary efficacy endpoints and exploratory endpoints
 
The same approach as for primary endpoint will be used for analysis of secondary efficacy endpoints and exploratory endpoints, and completely similar hypotheses are be formulated as for the analysis of the primary endpoint. Mixed effects models will be used to analyze the change in values from baseline, adjusted for covariates and baseline estimates. No sensitivity analysis will be performed for secondary endpoints. No adjustments will be made for multiple comparisons, hypotheses will be tested hierarchically, hypothesis testing by secondary endpoints will be taken into account if statistically significant differences between groups for the primary endpoint are confirmed.
 
For all comparisons, a critical significance level of 0.05 was chosen.
 |

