Study is powered to claim superiority of MLC901 over Placebo by primary endpoint for following statistical hypothesis:  $H_0: LSM_T \geq LSM_R$ ,  $H_1: LSM_T < LSM_R$ , where  $LSM_T$  is a Least Square Mean of Change from Baseline of Complex attention score after 6 months of treatment assessed by the mixed model repeated measures analysis in the MLC901 group and  $LSM_R$  is a Least Square Mean of Change from Baseline of Complex attention score after 6 months of treatment assessed by the mixed model repeated measures analysis in the Placebo group (lower score of Complex attention is better).

PASS 14 software (Scenario: two sample T-test assuming equal variance) was used to estimate the required sample size. Target power – 80%. Alpha – 0.05. Proportion of subjects in groups – 1:1.

Hypotheses: H0:  $MT \geq MR$ , H1:  $MT < MR$ , where MT is an arithmetical mean of change of Complex attention score after 6 months of treatment, compared to baseline, in the MLC901 group, and MR is an arithmetical mean of change from baseline of Complex attention score after 6 months of treatment in the placebo group (lower score of Complex attention is better).

An estimate of 20 was obtained from the BRAINS pilot study (21) for standard deviation of change in complex attention from baseline to 6 months, 128 subjects (64 per arm) are required to detect a clinically meaningful difference of -10 in the mean changes in complex attention between MLC901 and placebo arms with 80% power at a two-sided 5% significance level. Sensitivity analysis: 1) power is equal 29% if the mean difference of primary estimate is 5 and power is equal 99% if the mean difference of primary estimate is 20; 2) power is equal 15% if the standard deviation increases up to 30, so some uncertainty in the standard deviation estimate may cause insufficient actual power for comparison.

The sample size is increased to 182 randomized subjects (91 per arm) to allow for 30% dropouts. Considering very high screening failure rate up to 364 subjects can be screened.

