### **9.3 Level of Significance to be Used**

The two-sided significance level of 0.05 (5%) will be applied for all statistical tests.

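### The stated hierarchy ends at the gate from primary to secondary endpoints: five or six secondary tests then run at 5% each, with no order, stop rule or alpha split

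*Protocol*

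**What the plan says.** The multiplicity rule is at the end of protocol Section 9.1.2 and is repeated in the synopsis (Section 1.2, statistical methods): "No adjustments will be made for multiple comparisons, hypotheses will be tested hierarchically". The same sentence goes on to describe what the hierarchy consists of: "hypothesis testing by secondary endpoints will be taken into account if statistically significant differences between groups for the primary endpoint are confirmed". No further step is given.

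The secondary endpoints in Section 9.1.2 are two bullets. The first covers the remaining CNS-VS domains: "executive functioning, processing speed, memory (visual and verbal) and reaction time". The second is the symptom score: "Change in the Rivermead Post Concussion Symptoms Questionnaire (RPQ) total score, after 6 months of treatment". The protocol never says how many hypotheses this makes. Counting visual and verbal memory separately gives six; counting memory as one score gives five.

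Each of these endpoints gets its own formal hypothesis, since "completely similar hypotheses are be formulated as for the analysis of the primary endpoint". The level is set once for everything. Section 9.3 says "The two-sided significance level of 0.05 (5%) will be applied for all statistical tests", and the synopsis says "For all comparisons, a critical significance level of 0.05 was chosen".

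Nowhere does the protocol name a testing order among the secondary endpoints, say that testing stops after a failure, or divide alpha.

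**The concern.** A hierarchical procedure can dispense with alpha adjustment when the order of the tests is fixed in advance and testing stops at the first non-significant result. Each hypothesis is then tested at full alpha only if everything before it succeeded. The protocol invokes the hierarchy but supplies only its first rung, from the primary to the secondary family. Within the family, every member may be tested at 5% whatever happens to the others.

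This matters in the situation where the secondary results will be read most closely, namely when complex attention is significant because MLC901 really affects it. The gate is then open and no longer limits anything. If the effect is confined to complex attention, the number of chances to find a spurious benefit elsewhere is the number of secondary tests, and the stated rule does nothing to limit it.

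**Working it through.** **Inputs.** Two-sided 0.05 per test (Section 9.3, synopsis). Number of secondary tests k = 6, or 5 if memory is one score (Section 9.1.2). Primary design: difference 10, SD 20, 80% power, 1:1 allocation (Section 9.2). The correlation between test statistics is not given, so 0 to 0.8 is assumed, equal for all pairs.

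**The plan's own figure.** The protocol states no error rate for the secondary family; the only figure tied to alpha is the primary sample size. By the normal approximation, n per arm = 2 × (1.96 + 0.84)² × 20² / 10² ≈ 63. The two-sample t-test gives 63.8, so 64 per arm, with power 80.1%. This reproduces the protocol's statement that "128 subjects (64 per arm) are required to detect a clinically meaningful difference of -10 in the mean changes in complex attention". The calculation uses the primary test alone, so nothing below changes it.

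**Primary null true.** The gate opens in favour of MLC901 with probability 2.5%. The chance of passing it and then having any false secondary result cannot exceed that. By simulation with all nulls true and k = 6, it is 0.7% (independent) to 2.0% (correlation 0.8). The gate works in this case.

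**Primary effect real, all secondary nulls true, gate taken as open.** If the tests are independent:

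- either direction, k = 6: 1 − 0.95⁶ = 26.5%
- either direction, k = 5: 1 − 0.95⁵ = 22.6%
- favouring MLC901 only, k = 6: 1 − 0.975⁶ = 14.1%
- favouring MLC901 only, k = 5: 1 − 0.975⁵ = 11.9%

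With equally correlated normal test statistics (one million simulated draws):

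| Assumed correlation | Favouring MLC901, k = 6 | Either direction, k = 6 | Either direction, k = 5 |
|---|---|---|---|
| 0 | 14.1% | 26.5% | 22.6% |
| 0.3 | 12.2% | 24.1% | 20.9% |
| 0.5 | 10.4% | 20.7% | 18.2% |
| 0.7 | 8.2% | 16.5% | 14.9% |
| 0.8 | 7.0% | 13.9% | 12.7% |

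The reference value is 2.5% for the favourable column and 5% for the other two.

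**Allowing for a gate that opens with only 80% power.** The joint probability that the gate opens and at least one of six secondary tests is falsely significant in either direction is 0.80 × 26.5% = 21.2% if independent, 10.0% at correlation 0.7 and 7.6% at 0.8. Counting only results favouring MLC901, it is 11.3% if independent and 8.2% at 0.7. The favourable figures change little, because a favourable primary and favourable secondary results tend to occur together when correlated.

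**What the remedies give.** In a fixed sequence, a false claim requires rejecting the first true null in the order, so the chance of any false claim is at most 5% two-sided. Holm across six starts at 0.05/6 = 0.0083 (0.01 for five). When all six nulls are true, the chance of any rejection is 1 − (1 − 0.0083)⁶ = 4.9% if independent and 2.8% at correlation 0.8.

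**The case against.** The best counter-argument is that this is detail left to the SAP. Section 9.1 promises a comprehensive SAP before data lock or unblinding, and full alpha at each test with no adjustment is exactly how a fixed-sequence procedure would be described. An SAP that named an order and a stop rule would close the gap. That stands as far as it goes: the protocol does not rule out such an SAP, and the SAP is not among the documents examined. But the protocol is not silent. It decides that nothing is adjusted, spells out the hierarchy as the primary gate, and puts every comparison at 5%. An analyst who follows that text tests an unordered family.

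A second objection is to the size. The hypotheses are directional, so a false efficacy finding is one that favours MLC901. The CNS-VS domains come from one test battery and are unlikely to be independent. Both points are right. They are why the favourable-direction range is the one to lead with and why 26.5% is only the upper end of the two-sided range.

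A third is that the protocol defines a superiority claim explicitly only for the primary endpoint. Secondary tests are merely to be taken into account, and the amendment log in Section 18 shows that wording calling the secondary analysis confirmatory belonged to the replaced text. A reader might infer that false secondary findings are planned to be presented as confirmed; the current text does not say so. It does give each secondary endpoint a hypothesis of the same form as the primary and makes its use conditional on the primary, so a claim is not excluded either. That ambiguity is part of what needs settling.

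**Conclusion.** The concern holds in a limited form. As written, the protocol controls secondary error when the primary null is true but not among the secondary endpoints when the primary effect is real. In that case, with all six secondary nulls true, the chance of at least one false result favouring MLC901 is about 8% to 14%, against 2.5% for one test. In either direction it is about 16% to 26%. Both ranges run over assumed correlations of 0.7 to 0 and take the gate as open. With five endpoints the conclusion is the same (11.9% and 22.6% if independent).

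Two stronger readings are not supported. One is that the hierarchy gives no protection at all; the gate does protect when the primary null is true. The other is that the trial's main conclusion is at risk; the primary test's type I error, power and sample size do not depend on how the secondary endpoints are tested. The defect is worth correcting before unblinding and does not threaten the design.

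**What to change.** Before unblinding, list the secondary hypotheses one by one in Section 9.1.2 and the synopsis, settling whether memory is one score or two. Then choose one of the following:

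- **Fixed sequence.** Test in a pre-stated order, each at two-sided 5%, stopping at the first non-significant result. The order is the sponsor's choice. The document supports executive functioning first, since Section 2.3.2 reports a pilot result for it (P = 0.04).
- **Holm across the family**, applied once the primary is significant.
- **No claim.** State that secondary p-values are nominal and support no formal claim.

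The change takes a few sentences and no extra patients. Under a fixed sequence, endpoints late in the order may not support a formal claim even if their own p-value is small. Under Holm, those with weaker evidence may not. For scale, at the strictest threshold of 0.0083, a standardized effect of 10/20 = 0.5 with 64 per arm has 56% power, against 80.1% at 0.05. That effect is borrowed from the primary endpoint, since the documents give none for the secondary endpoints. It is plain Bonferroni power, and Holm is never less powerful than Bonferroni.
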